#### Secondary objectives

To test the secondary and tertiary aims that the ER class will have greater reductions in pain bothersomeness, sleep disruption, pain intensity, anxiety, depression, and physical function compared to WLC, our primary endpoint will be considered at 1 month post-treatment, and its within-subject difference from baseline will be calculated. The mean difference in the ER group will be compared against the WLC arm using the two-sample *t* test. Similarly, we will also compare the proportion of success rate, defined as ≥30% reduction in our outcomes for a clinically significant treatment response [52].

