**Discussion:**

This study aims to test the utility of a single-session videoconference-delivered group pain education class to improve self-regulation of pain and pain-related outcomes. Findings from our project have the potential to significantly reduce barriers to effective psychological treatment for pain, optimizing the delivery of increasingly vital online and remote-delivered intervention options.

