## Specific aims

Our specific aim and three corresponding hypotheses are outlined below.
We will conduct a randomized controlled trial comparing the preliminary effects of a single-session videoconference-delivered pain education class compared to a waitlist control (i.e., usual care) condition.
Hypothesis 1: The single-session intervention (Empowered Relief (ER)) will lead to greater reductions in pain catastrophizing compared to a usual care condition.Hypothesis 2: ER will lead to greater reductions in pain bothersomeness and sleep disturbance compared to a usual care condition.Hypothesis 3: ER will lead to greater reductions in pain intensity, anxiety, depression, and physical function compared to a usual care condition.

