## Methods/design

### Overview

We are piloting a randomized clinical trial in which individuals with a chronic pain condition are randomly assigned to one of two arms: a single-session videoconference-delivered group pain education class or a waitlist control (WLC) receiving usual care (Figs. 1 and 2). Participants will be followed for 3 months after treatment. Participants will be assessed via an online screening form, a phone screening, enrollment survey, 2-week follow-up, and at 1, 2, and 3 months post-treatment. Team statisticians blinded to participant treatment assignment will assess the outcomes 2 weeks after treatment and after 1, 2, and 3 months. The primary outcome is pain catastrophizing 1 month post-treatment. Secondary outcomes include reductions in pain bothersomeness and PROMIS sleep disturbance at 1 month post-treatment. Tertiary outcomes include reductions in pain intensity, PROMIS anxiety, PROMIS depression, and PROMIS physical function. The protocol for this trial has been approved by the Stanford Institutional Review Board (IRB). All participants will be required to give informed consent to a trained study team member prior to enrollment in the study.

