### Measures

Demographic data, pain characteristics, and physical and psychosocial health measures will be collected at enrollment. Pain catastrophizing will be assessed using the Pain Catastrophizing Scale [38]. Pain bothersomeness will be assessed by a single-item question that is commonly used in chronic low back pain research [39, 40]. PROMIS measures will be used to assess sleep disturbance, pain intensity, pain interference, physical function, depression, and anxiety using short forms [41]. Our group has applied the NIH PROMIS measures in multiple nationally funded clinical pain treatment trials and other studies [42–44] (Table 3).

**Table 3 Tab3:** Baseline and follow-up measures

Measurement	Brief measure description	Baseline Pre-class survey	Follow-up week 1 (ER class only)	Post-treatment Week 2	Post-treatment Months 1, 2, and 3
Demographics	Date of birth, gender, ethnicity, race, education level, household income, employment, and marital status.	x			
Pain Catastrophizing Scale (PCS) [31]	13-item scale assesses the severity of trait pain catastrophizing tendencies on a 5-point scale (0 = “not at all”; 4 = “all the time”); sum scores range from 0 to 52. The PCS has 3 factors (helplessness, magnification, rumination) and has good psychometrics [31]. Higher score reflects more catastrophizing.	x		x	x
PROMIS measures [27]	NIH PROMIS measures will be used to assess multiple variables of interest, including pain intensity, pain interference, physical function, depression, anxiety, sleep disturbance, social isolation, anger, and fatigue. Short form 4- to 8-item measures will be used to minimize participant burden.	x		x	x
Pain bothersomeness	Single-item measure of pain bothersomeness in the past week from “not at all bothersome” to “extremely bothersome.”	x		x	x
COVID-19	4-item if tested negative and 9-item if tested positive for COVID-19. Assess how the coronavirus impacts chronic pain, day-to-day life, depression, and psychological health.	x			x
Satisfaction with treatment and Zoom (ER group only)	ER group will answer a 13-item survey that assesses the class experience and using Zoom (video-conferencing) as it relates to engagement, relevancy, and usefulness.		x		
Skill use (ER group only)	ER group will answer 5 questions assessing the frequency of skills use learned in class over the past week, from “not at all” to “several times a day.”		x		

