##### Tertiary outcome measures

NIH PROMIS measures [41] will be administered to assess pain intensity, anxiety, depression, and physical function. These measures have been successfully applied to pain research [45–48].

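### Physical function is listed among outcomes expected to fall, so the 30% responder rule as written would count loss of function as treatment success

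*Protocol article*

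**What the plan says.** Three sections of the protocol article give a direction for physical function, and all three give the same one.

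- Specific aims, Hypothesis 3: "ER will lead to greater reductions in pain intensity, anxiety, depression, and physical function compared to a usual care condition".
- Overview: "Tertiary outcomes include reductions in pain intensity, PROMIS anxiety, PROMIS depression, and PROMIS physical function".
- Statistical analyses, Secondary objectives: the aim is to show "greater reductions in pain bothersomeness, sleep disruption, pain intensity, anxiety, depression, and physical function compared to WLC".

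Secondary objectives then gives two analyses of change from baseline at 1 month. The first is on means: "The mean difference in the ER group will be compared against the WLC arm using the two-sample *t* test". The second compares success proportions, with success "defined as ≥30% reduction in our outcomes for a clinically significant treatment response". Neither makes an exception for physical function.

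The section on tertiary outcome measures names the instrument without a direction: "NIH PROMIS measures [41] will be administered to assess pain intensity, anxiety, depression, and physical function". The only scoring direction in the article is the one for the Pain Catastrophizing Scale (PCS) in Table 3: "Higher score reflects more catastrophizing".

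**The concern.** Five of the six outcomes in the Secondary objectives list are symptoms or complaints, for which a fall is a benefit. The sixth, physical function, is a capacity, for which a fall is a harm. Putting it under the shared noun has two consequences.

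First, Hypothesis 3 taken literally is supported for physical function only if ER lowers function more than usual care does. Second, the responder rule inherits the direction: a participant who loses enough function is a success, and one who gains as much is not.

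The responder rule matters more, because it is an operational definition that a programmer could apply as it stands. The article's Discussion also presents the proportion of patients reaching a meaningful reduction in several pain-related indices as something the trial will deliver. If the error is found only after the data are seen, correcting it means reversing a published success definition post hoc.

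**Working it through.** **Is the direction stated correctly anywhere?** The hypothesis, the outcome definition and the analysis rule all say reduction. The tertiary-measures section is silent on direction, so no correct statement overrides the other three. The abstract's Discussion gives the general intent, to "improve self-regulation of pain and pain-related outcomes", and a hypothesised loss of function conflicts with that.

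**Could a reduction be right because of the scoring?** Only if the form were scored so that a higher number means worse function. The article does not say so. Its only scoring direction is for the PCS, where higher is worse and a reduction is correctly a benefit. The check below therefore rests on the plain meaning of the name, with higher taken as better function.

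**What the responder rule does to one participant.** The article gives no baseline for physical function, so 40 is assumed.

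- 30% fall: 0.7 × 40 = 28, counted as success.
- 30% rise: 1.3 × 40 = 52, counted as failure.

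**What it does to the arm comparison.** All inputs are assumptions for illustration: baseline 40 for everyone, normally distributed change, SD of change 5 to 8, mean change +3 in ER and 0 in the waitlist control (WLC). The 30% threshold is 0.3 × 40 = 12 points.

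Rule as written, P(change ≤ −12) = Φ((−12 − mean)/SD):

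- ER: Φ(−15/5) = 0.1% at SD 5; Φ(−15/8) = 3.0% at SD 8.
- WLC: Φ(−12/5) = 0.8% at SD 5; Φ(−12/8) = 6.7% at SD 8.

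Rule in the direction of improvement, P(change ≥ +12) = 1 − Φ((12 − mean)/SD):

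- ER: 1 − Φ(9/5) = 3.6% at SD 5; 1 − Φ(9/8) = 13.0% at SD 8.
- WLC: 0.8% at SD 5 and 6.7% at SD 8, as above by symmetry.

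In this example ER truly improves function. The rule as written gives it fewer successes than the control; with the direction corrected it has more.

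**What it does to the mean comparison.** The t test compares mean within-subject change between arms. The estimate, mean change in ER minus mean change in WLC, takes its sign from the data: in the example it is 3 − 0 = +3 however the hypothesis is worded. A two-sided p-value is also the same under either wording. The article does not state sidedness. Only a one-sided test run in the literal direction of Hypothesis 3 would be affected.

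**What it does to the rest of the design.** The sample size (120 enrolled, 58 completers per group) is set for pain catastrophizing, so correcting this wording changes neither the sample size nor the power.

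**The case against.** The strongest reply is that this is one list sharing one noun, repeated in three sentences, and not a decision to treat deterioration as benefit. The trial's purpose is plainly improvement, and an analyst would probably handle function correctly. The responder comparison is an additional analysis of one tertiary outcome in a pilot. The numerical example also depends on a scoring direction and a baseline that the article does not give.

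Most of this stands, and it limits the severity. It does not make the text right: the responder rule is stated without exception, and no section supplies a correct direction. An analysis plan that is not shown might handle function properly, but it would then contradict the published article.

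A reader might infer more, namely that the mean comparison also has the wrong sign and that the published result for physical function would come out reversed. The article does not support that. It specifies no contrast direction or one-sided test that would turn the estimate round, and a reported mean change would carry its true sign. For the mean comparison, only the stated hypothesis is wrong.

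**Conclusion.** The point holds in a limited form. Hypothesis 3, the tertiary outcome definition and the Secondary objectives all state the benefit for physical function in the wrong direction, and the 30% responder rule, applied as written, would count loss of function as success. This affects one of the six secondary and tertiary outcomes: its stated hypothesis and its responder definition.

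The conclusion rests on the plain meaning of physical function and would fail only if the form were scored as impairment, which the article nowhere says. The percentages above illustrate the mechanism under assumed inputs; they do not predict this trial's results. Severity is minor to moderate.

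**What to change.** In Specific aims (Hypothesis 3), Overview and Secondary objectives, take physical function out of the list of reductions and state that ER is expected to give greater improvement in it, that is, an increase if higher scores mean better function. State the scoring direction of the form once, for example in Table 3 beside the one already given for the PCS. In Secondary objectives, limit the reduction-based success rule to the symptom outcomes and define the physical function responder in the direction of improvement.

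The cost is a few words in three sections, one scoring statement, and a check that the responder program uses the same direction. It should be done before the outcome data are analysed, so that the change cannot be read as a response to the results.

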##### Secondary outcome measures

Our secondary outcome is pain bothersomeness, whereby participants rate their chronic pain bothersomeness during the previous 7 days on a 0 to 10 numeric rating scale anchored by 0 (not at all bothersome) and 10 (extremely bothersome) that is commonly used in CLBP research [39, 40]. PROMIS sleep disturbance will be assessed with the NIH PROMIS sleep disturbance short form.

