## Discussion

In this trial, we will seek to determine whether a group-based single-session intervention (SSI) that is delivered online is an effective treatment option for persons with chronic pain. In 2019, the US Health and Human Services cited “Empowered Relief” as a promising scalable behavioral pain treatment [53], and for the first time, this study aims to test whether a videoconference-delivered version of the class may similarly effectively and efficiently reduce the burden of chronic pain and improve symptom management. Importantly, it addresses the rapidly expanding need for alternatives to face-to-face encounters due to the COVID-19 pandemic. Finally, the study will identify a proportion of patients who achieve a meaningful reduction in a number of pain-related indices in response to this online single-session intervention. This will facilitate the future application of the digital version of the class across a variety of settings, such as in primary care or in pre-surgical populations, and possibly across chronic health conditions with a primary pain complaint.

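### One 30% reduction rule is applied to five PROMIS outcomes whose scoring metric is not stated, so their success rates depend on where the chosen scale starts

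*Protocol article*

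**What the plan says.** The Secondary objectives section of the protocol article covers the hypothesis of "greater reductions in pain bothersomeness, sleep disruption, pain intensity, anxiety, depression, and physical function compared to WLC". It specifies a two-sample t test on change from baseline at 1 month and adds a comparison of success rates, with success "defined as ≥30% reduction in our outcomes for a clinically significant treatment response". One threshold, in relative form, therefore serves all six outcomes.

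Five of the six are PROMIS scores. Under Secondary outcome measures, "PROMIS sleep disturbance will be assessed with the NIH PROMIS sleep disturbance short form". Under Tertiary outcome measures, "NIH PROMIS measures [41] will be administered to assess pain intensity, anxiety, depression, and physical function". On the instruments themselves, Table 3 says "Short form 4- to 8-item measures will be used to minimize participant burden". The article does not say whether the analysed score is a raw sum or a standardized T-score, how items are coded, or what the lowest possible score is.

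Two outcomes are described differently. For the PCS, Table 3 states that "sum scores range from 0 to 52", and bothersomeness is a 0 to 10 rating under Secondary outcome measures. Both have a stated zero.

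The Discussion says that "the study will identify a proportion of patients who achieve a meaningful reduction in a number of pain-related indices".

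**The concern.** A percentage reduction has a stable meaning when zero on the scale stands for absence of the symptom. On a scale with any other origin, the percentage is taken of a quantity that includes an arbitrary constant. Moving that constant changes who counts as a success although no patient's answers have changed.

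At stake is what the PROMIS success rates can tell a reader. Depending on the metric, the same benefit could appear as almost no responders or as a large fraction of the arm. Near-zero rates in both arms could be misread as lack of benefit. If the metric were still open when results are seen, the choice could also move the result. The threshold and its scope are fixed in the text, so an analysis plan that applied them as written would inherit the problem even if it named the metric.

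**Working it through.** **Plan's own figure.** The article gives no expected success rate and no power for the success-rate comparison, so there is nothing to reproduce on this point. The arm size used below, 58 completers, comes from Sample size and detectable differences.

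**1. Dependence on the origin.** Let B be the baseline score, F the follow-up score and c the constant removed by recoding. The percentage fall is (B - F)/B before recoding and (B - F)/(B - c) after it. Item coding is not in the article; 1-5 and 0-4 are assumed.

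| Form | Coded 1-5 | Fall | Same answers coded 0-4 | Fall |
|---|---|---|---|---|
| 4 items | 12 to 9 | 3/12 = 25% | 8 to 5 | 3/8 = 37.5% |
| 8 items | 24 to 18 | 6/24 = 25% | 16 to 10 | 6/16 = 37.5% |

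In each row the patient fails under one coding and succeeds under the other.

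**2. T-score metric (assumed: reference mean 50, SD 10).** Required drop = 0.30 × B.

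| Baseline | Drop needed | In reference SDs |
|---|---|---|
| 50 | 15.0 | 1.50 |
| 55 | 16.5 | 1.65 |
| 60 | 18.0 | 1.80 |
| 65 | 19.5 | 1.95 |
| 70 | 21.0 | 2.10 |

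On this metric zero lies 50/10 = 5 SDs below the reference mean, which is why 30% of the score is such a large change.

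**3. How many would respond on T-scores.** Take baseline and follow-up as bivariate normal with common SD s, correlation r, baseline mean μ and mean change m. Success means F ≤ 0.7B, so

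P(success) = Φ( -(0.3μ + m) / √(s²(1.49 - 1.4r)) ).

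The assumed grid is μ = 55, 60, 65; s = 7, 9; r = 0.60, 0.75; m = 0, -3, -5.
- Highest value (μ = 55, s = 9, r = 0.60, m = -5): 0.3 × 55 - 5 = 11.5; √(81 × 0.65) = 7.26; Φ(-1.585) = 5.65%.
- Lowest value (μ = 65, s = 7, r = 0.75, m = 0): 0.00% to two decimals.
- Of the 36 combinations, 33 are below 3%.

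Of 58 patients, 5.65% is about 3.

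**4. One simulated benefit, three scorings.** The assumed latent improvement is 0.525 SD in the class arm and 0 in the waitlist arm, with correlation 0.65. T-scores have mean 58 and SD 8. The 4-item raw sum has mean 11 and SD 3.5, rounded and kept within its limits. Power is for 58 per arm.

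| Scoring | Class arm | Waitlist arm | Power |
|---|---|---|---|
| T-score | 1.5% | 0.2% | about 0.12 (normal approximation poor) |
| Raw sum, items 1-5 | 28.7% | 10.9% | 0.67 |
| Raw sum, items 0-4 | 45.4% | 21.5% | 0.78 |

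The success rate in the class arm runs from about 1% to 45% through the scoring alone.

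**The case against.** The strongest reply is that the article never mentions T-scores or item coding, and that choosing a metric is a detail an article commonly leaves to the full protocol or analysis plan. This stands as far as it goes. Every T-score and raw-sum figure above is conditional, and the silence on the metric is not itself the fault. The fault is the stated rule, whose meaning changes with that choice.

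A reader might infer that the rule is unattainable on PROMIS scales, or that the share of patients with meaningful improvement cannot be determined for these outcomes. The article does not support either reading. Even on T-scores the result is rare response, not impossible response, and on raw sums the simulated comparisons are usable. The Discussion speaks of a number of indices, not all of them, and the PCS and bothersomeness can supply those. Specific aims contains no responder objective.

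It is also tempting to object that patients near the floor of a raw sum cannot succeed: from 5 on a 4-item form the best fall is 1/5 = 20%, and from 11 on an 8-item form 3/11 = 27.3%. This carries little weight. Such patients have few symptoms to lose, and a PCS score of 0 cannot fall by 30% either.

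Nor should the 15 to 21 points be set against the group difference the trial can detect. One is a change within a patient on PROMIS. The other is a difference between arm means, and the article discusses power only for the PCS.

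Finally, the success rates support the t tests, and this is a pilot. That limits the consequence but does not remove the inconsistency.

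**Conclusion.** The concern holds in a limited form. A single relative threshold is fixed for outcomes of which five have no stated zero-anchored range, and for those five the success rate depends on the scale's origin. That dependence follows from arithmetic alone. Its size rests on assumptions: about 0 to 6% responders if T-scores are used, with the baselines, SDs, correlations and mean changes listed, and otherwise a usable comparison whose level shifts with the item coding.

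The primary t test, the PCS success rule in Primary analyses, the bothersomeness rule and all mean-change tests are untouched. A PROMIS pain intensity item scored from zero would escape too. The effect is confined to supportive analyses, but the correction is cheap enough to make before the data are analysed.

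**What to change.** Limit the 30% rule to zero-anchored scales: the PCS and the 0 to 10 ratings. For each PROMIS score, name the metric to be analysed and prespecify a fixed point change, in the direction that means improvement for that score, as the definition of success. The size of that change should be justified on measurement grounds for the instrument, not taken from the difference the trial is powered to detect. The article contains nothing from which a particular value could be derived, so the sponsor must supply and support one. Alternatively, drop the PROMIS success rates and report mean differences only.

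Either route costs about a sentence in the analysis section and needs no new data. The downside is that success is no longer defined identically across outcomes, so success rates should not be compared between the PROMIS scores and the zero-anchored scales.

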## Discussion

In this trial, we will seek to determine whether a group-based single-session intervention (SSI) that is delivered online is an effective treatment option for persons with chronic pain. In 2019, the US Health and Human Services cited “Empowered Relief” as a promising scalable behavioral pain treatment [53], and for the first time, this study aims to test whether a videoconference-delivered version of the class may similarly effectively and efficiently reduce the burden of chronic pain and improve symptom management. Importantly, it addresses the rapidly expanding need for alternatives to face-to-face encounters due to the COVID-19 pandemic. Finally, the study will identify a proportion of patients who achieve a meaningful reduction in a number of pain-related indices in response to this online single-session intervention. This will facilitate the future application of the digital version of the class across a variety of settings, such as in primary care or in pre-surgical populations, and possibly across chronic health conditions with a primary pain complaint.

